## **17.3 Distress Protocol**

There may be some distress and burden in completing the questionnaires and taking part in the study. However, it is also found that many patients and families value taking part in research and want to have the opportunity to give their view. We have found that including the opportunity for open comments, not only gives rich supplementary research data, but is highly valued by patients and families as they feel 'heard' by those researchers [57-60]. Therefore we have incorporated this approach into our study. All research nurses and those conducting interviews will be centrally trained and supported in the work and we will ensure that all have appropriate prior experience (such as in palliative or neurological care). All of the research team will have completed Good Clinical Practice training, and specific training on addressing distress in palliative care. Research nurses will follow a distress protocol if patients or families become upset during the interviews or are found to be upset or in distress on arrival. Should this be the case they will first offer to pause, postpone

or stop the interview and advise again that participation is voluntary. In the case of severe distress the patient will be encouraged to share his or her feelings with a member of their healthcare team or the nurse offers to contact the neurology team. We anticipate distress caused by the research will be very infrequent, given the general nature of the questions within the measures used, and is likely to reflect advanced disease and not the questionnaires themselves. If participants disclose any ideation of self-harm or other risk to themselves or others, this will be dealt with as an urgent matter and clinical help will be sought. This will be in agreement with the participant however, if the research team believes the participant is at imminent risk and refuses to allow voluntary disclosure, the research team will breach confidentiality. Based on prior experience, we anticipate this will be a very rare occurrence. Provision will be made to ensure the researchers have PI or senior back up available by phone whenever they are undertaking data collection. We make it clear that patients and families can omit any questions they don't want to answer and can withdraw at any time from the service and the study with no effect on their usual services. We have ensured that we do not include terms that might be distressing, such as "end of life" or "prognosis", on the information leaflets or questionnaires. The palliative care service likewise takes a listening and individual approach, so that patients who may not want to talk about issues in relation to care, but want symptom support, can receive those elements of the service they want.

### **17.4 Qualitative component**

Integrated within the trial is a qualitative component, to explore: (A) how the intervention is delivered in practice and (B) how the change process of SIPC may be working and which aspects of SIPC are most valued or impact most on patients and caregivers experiences of care and enhance the service model of SIPC. The methods build on those tested in our phase II trial [5 28 37 61]. We select a maximum variation sample of patients and caregivers who received SIPC (at week 12 for the intervention group and week 24 for the standard group) and health professionals in the study sites (e.g. community matrons, specialist nurses, primary care, neurologists). Case selection is based on socio-demographic variables (e.g. age, gender, educational level), neurological condition, severity of symptom presentation and change over time (baseline to 6 weeks or 12 to 18 weeks) in the primary outcome measure (IPOS Neuro-S8) to encompass patients with e.g. reduction symptom burden, no change, and increase. The qualitative interview schedule is informed by our phase II development work and previous literature [62 63] and explores the experiences of receiving SIPC, deductively (e.g. relevance of outcome measure change on daily life), and inductively (e.g. patient reported experiences of SIPC)[64]. All research nurses will be trained to conduct these interviews (after the 12 week data collection point for the immediate intervention and 24 week data collection point in the control group). If possible, we try to find a different interviewer to minimise the unblinding of research nurses. Research nurses will be trained in conducting qualitative interviewing. The interviews are digitally recorded and transcribed and anonymised prior to analysis [65]. We will pilot the qualitative interview during the set-up phase.

Non-patient focus groups are conducted with providers and commissioners from different sites to explore the perceptions of SIPC, the local contexts and processes of SIPC delivery and implementation. They are identified by research teams from different sites, who will provide the research team at King's College London with a list. The research team will approach professionals via email. The focus groups are incorporated in to project workshops with providers and commissioners, for example, training days, project updates. This minimises participants' time away from practice, and maximises opportunities to understand the context and description of practice and integration with SIPC. Each group comprises representatives from the respective sites and disciplines involved in the care provision. Where attendance at a focus group is not possible, individual interviews are conducted (either face-to-face or by telephone) in order to accommodate the busy schedules of healthcare professionals and allow representation from all sites. The groups are facilitated by a single researcher experienced in qualitative research methods and an observer (applicants [name] and [name] are both experienced in qualitative methods) to document, for example, group processes and interactions. The groups are digitally recorded, transcribed and anonymised prior to analysis [65].

### **17.5 Survey of health professionals**

The survey of health professionals will be a brief questionnaire distributed both at the beginning and at the end of the intervention, focussed on their expectations/views of SIPC, how it has or has not affected the process of care, how it might be improved and ways to best meet the needs of patients and families with LTNCs. It will be offered via e-mail, with data collected using a web based tool (e.g. Keypoint), and space for open comments. Research teams at the different sites will identify the neurology and palliative care team members involved in the intervention and provide an email list to the research team at King's College

London. The researcher will be sending out the survey, with up to 2 reminders. If surveys are completed, informed consent is assumed. This will be detailed on the information sheet.

**Figure 3: Summary schedule of study**

| Timeline                                                                  | Fast track (immediate referral to palliative care service) | Standard care (waiting list control) |
|---------------------------------------------------------------------------|------------------------------------------------------------|--------------------------------------|
| Consent and Baseline interview                                            | a                                                   | a                             |
| Randomisation                                                             |                                                            |                                      |
| 2 working days from receiving information about patient                   | b                                                   |                                      |
| 1-6 weeks                                                                 | c                                                   |                                      |
| 6 weeks                                                                   | d                                                   | d                             |
| 6-8 weeks                                                                 | e                                                   |                                      |
| 12 weeks                                                                  | f                                                   | f                             |
| 2 working days after receiving research nurse data from week 12 interview |                                                            | g                             |
| 12-18 weeks                                                               | h                                                   | i                             |
| 18 weeks                                                                  | j                                                   | j                             |
| 18-20 weeks                                                               |                                                            | k                             |
| 24 weeks                                                                  | l                                                   | l                             |
| 24-26 weeks                                                               |                                                            | h                             |

|          |                                                                                                                             |
|----------|-----------------------------------------------------------------------------------------------------------------------------|
| a | Baseline research interview and consent on entry to the study before randomisation                                          |
| b | Palliative care assessment within 2 working days                                                                            |
| c | Palliative care team care, including assessment, treatment, referral                                                        |
| d | Research interview at 6 weeks after randomisation                                                                           |
| e | Palliative care team care continues usually ending by 6-8 weeks, with referral on for those patients needing long-term care |

|          |                                                                                                                                                |
|----------|------------------------------------------------------------------------------------------------------------------------------------------------|
| f | Research interview at 12 weeks after randomisation                                                                                             |
| g | Standard care group now offered palliative care team who see person within 2 working days of receiving information                             |
| h | Patients now discharged from palliative care team, if have been referred on some under care of community team, which continues from this point |
| i | Palliative care team now providing care in standard care group, following their 12 week wait                                                   |
| j | Research interview at 18 weeks                                                                                                                 |
| k | Palliative care team care continues usually ending by 6-8 weeks, with referral on for those patients needing long-term care                    |
| l | Final research interview at 24 weeks after randomisation                                                                                       |

## 18. Assessment of Efficacy

### 18.1 Primary Efficacy Parameters

Primary efficacy parameter is the combined score of eight key symptoms as measured by the IPOS Neuro-S8 at 12 weeks. This is (based on) a validated scale used among people with LTNCs that is shown to be responsive to change. We have chosen this primary outcome based on the results of the phase II trial and our modelling work: patients consider these are all important symptoms in neurological conditions; the SIPC aims to improve several complex symptoms which interact; these symptoms are often overlooked by existing services but impact on quality of life; this measure was more responsive to change than the quality of life measure. Psychometric properties of the five items of the IPOS Neuro-S (IPOS Neuro-S5) tested in the control group of MS patients in our phase II trial found that it correlated well at baseline with the much longer MSIS-29 (Spearman rho=0.74), although the correlation reduced over time, as scores on the MSIS deteriorated or were missed. Internal consistency, indicated by Cronbach's alpha, for baseline assessments was 0.82, a good value for a 5-item scale. Test-retest reliability of scores over two assessments (where patients did not receive the intervention and were assumed to be more stable) showed an Interclass Correlation Co-efficient (ICC) of 0.81. Similar properties are found when the IPOS Neuro-S5 is tested in patients with PD. In a sample of 82 patients, ICC over two assessments was 0.72. We have used the IPOS Neuro-S5 among people severely affected by many conditions (cancer, renal, MS, PD, PSP, MSA, and in both randomised controlled trial and longitudinal observational study design [28 29 61 66]. The IPOS Neuro-S5 exhibited promising psychometric properties in our study samples, though it has not yet been validated in larger populations or in people affected by MND. However, this brief measure is so far the best we can use, given the floor effects of many measures among people severely affected by a long-term neurological conditions [66].

### 18.2 Secondary Efficacy Parameters

- 1) Patients' palliative needs and symptoms: Integrated Palliative care Outcome Scale for neurological conditions (IPOS Neuro) (based on a commonly used and well validated measure in palliative care research and clinical practice) [4 67-70];
- 2) Patients' health-related quality of life and well-being: EQ-5D and ICEpop CAPability measure for Adults (ICECAP-A) [71]. EQ-5D is a 5 item measure (mobility, self-care, usual activities, pain/discomfort, anxiety/depression) used to generate quality adjusted life years (QALYs). It has been used in numerous economic evaluations including those for neurological conditions. It will be the main measure in the cost-effectiveness analysis. The ICECAP-A is a new capability/well-being measure for use in economic evaluations. It has 5 items (feeling settled and secure; love, friendship and support; being independent; achievement and progress; enjoyment and pleasure) each scored 1-4 [72]. The possible states derived from the ICECAP-A are currently being valued in a way appropriate for QALY calculations (this will be completed before our analyses). QALYs generated will be used in secondary cost-effectiveness analyses; or the Integrated Palliative Outcome Scale for neurological conditions (IPOS Neuro);

- 3) Patients' psychological distress: Hospital Anxiety and Depression Scale (HADS) (patient reported);
- 4) Patients' satisfaction, self-efficacy and other aspects: patient satisfaction scale (modified FAMCARE-P16) [73], Self-Efficacy to Manage Chronic Disease Scale (SEMCD), an advance care planning scale (as used by Tuck et al 2013 [74]) and some questions covering patients' experiences of the study;
- 5) Hospital, service use and survival: hospital admissions, length of hospital stay and emergency attendances during the study and other health service use extracted from clinical records and also recorded using an adapted version of the Client Service Receipt Inventory (CSRI) at 0, 12, and 24 weeks [75]. The CSRI has been used in around 300 studies internationally. Services will include specialist palliative care, other primary and secondary healthcare, medication, social care, and care from family members. Where possible we will supplement CSRI data with data from hospital-based information systems. Employment status and welfare benefits will also be recorded. Survival (days from consent to death) for those patients who die irrespective of cause, will also be evaluated;
- 6) Caregiver assessment of patients' problems and service use: IPOS Neuro and CSRI (due to cognitive impairment for some patients, to be analysed separately from patient data);
- 7) Caregiver burden, positivity, quality of life and satisfaction: 12-item Zarit Burden Inventory (ZBI-12) and positivity [76], quality of life (VR12) [77] and the carer satisfaction scale (modified FAMCARE 2) (self-assessed by caregivers) [73 78];
- 8) Observer (completed by the researcher) assessment of the patients problems: Support Team Assessment Schedule (STAS), an observer rated assessment of palliative care problems – which has several items overlapping with the IPOS Neuro, and is designed for use through independent assessment [67].

**Table 1: Candidate questionnaires that may be used in the study**

| Reporter     | Domains assessed                                 | Questionnaire                                                                           |
|--------------|--------------------------------------------------|-----------------------------------------------------------------------------------------|
| Patient      | Symptoms & Palliative care Outcome               | 1. Integrated Palliative care Outcome Scale for neurological conditions (IPOS Neuro S8) |
|              | Quality of life & Well-being                     | 2. EuroQoL (EQ-5D)                                                                      |
|              | Psychological distress                           | 3. ICEpop Capability measure for Adult (ICECAP-A)                                       |
|              | Hospital & Healthcare service use & costs        | 4. Hospital Anxiety and Depression Scale (HADS)                                         |
|              | Satisfaction & other aspects                     | 5. Client Service Recipient Inventory (CSRI)                                            |
|              |                                                  | 6. Modified 16-item measure of patient satisfaction (FAMCARE-P16)                       |
|              |                                                  | 7. Self-Efficacy to Manage Chronic Disease Scale (SEMCD)                                |
|              |                                                  | 8. Advance Care Planning                                                                |
| Carer        | Proxy patient symptoms & palliative care outcome | 9. IPOS Neuro S8 – Carer                                                                |
|              | Caregiver burden & positivity                    | 10. 12-item Zarit Burden Inventory (ZBI-12) + positivity – Carer                        |
|              |                                                  | 11. Veterans Rand 12 item Health survey (VR-12) – Carer                                 |
|              | Hospital & Healthcare service use & costs        | 12. CSRI – Carer                                                                        |
|              | Satisfaction & other aspects                     | 13. Modified 17-item measure of carer satisfaction (FAMCARE2)                           |
| Professional | Cognitive impairment                             | 14. 6 item Cognitive Impairment Test (6CIT)                                             |
|              | Functional/Neurological disability               | 15. Barthel Index (BI)                                                                  |
|              |                                                  | 16. Modified Fried's Frailty Criteria                                                   |
|              |                                                  | 17. Northwick Park Dependency Scale (NPDS)                                              |
|              |                                                  | 18. Expanded Disability Status Scale (EDSS) – for MS                                    |
|              |                                                  | 19. Hoehn & Yahr Scale (H & Y) – for PRDs                                               |
|              |                                                  | 20. Bulbar or limb – for MND                                                            |
|              |                                                  | 21. Australian modified Karnofsky Performance Status                                    |
|              | Patient symptoms & PC outcome                    | 22. Support Team Assessment Schedule (STAS)                                             |
|              | Adverse Events                                   | 23. Adverse Events                                                                      |

\*MS: Multiple Sclerosis; PRDs: Parkinsonism & Related Disorders; MND: Motor Neurone Disease

In choosing these outcome measures, we have carefully selected scales to avoid significant floor and ceiling effects in a very disabled population. We have chosen measures that are simple and easy to use, and are not too lengthy, as the population cannot complete very long questionnaires. An observer rated measure is included to collect data among patients with cognitive impairment.

## 19. Assessment of Safety

### 19.1 Specification, Timing and Recording of Safety Parameters.

Number of deaths, emergency attendances, hospital admissions and length of hospital stay in each arm in total and by disease will be monitored. Any noticeable increase in these parameters will be subject to full investigation which will be acted upon.

### 19.2 Procedures for Recording and Reporting Adverse Events

We did not observe any harmful effect in our Phase II trial of SIPC among people severely affected by multiple sclerosis (MS). We are not expecting to see any harmful effect in this trial. However, we will monitor deaths, survival, hospitalisation, length of hospital stay and emergency attendance by trial arm and by diagnosis, and six-monthly report these statistics to the Data Monitoring Committee (DMEC) and Study Steering Committee (SSC).

### 19.3 Stopping Rules

Any one of the following:

- If the study cannot achieve a minimum of 25 recruited at 6 months from the start of recruitment to the study;
- If SIPC cannot be delivered to at least 80% of patients in the SIPC arm within 3 weeks of randomisation; more than 10% of patients in the control arm received specialist palliative care within 11 weeks of randomisation;
- If the DMEC and/or SSC raise any new safety or ethics concerns over the trial process and make recommendations to discontinue the trial;

These rules will be reviewed and approved by SSC and DMEC once these committees are formed. If the study is prematurely discontinued, active participants will be informed and no further participant data will be collected.

## 20. Statistics

### 20.1 Sample Size

Based on the data from our Phase II MS trial, the five centres altogether need to recruit 356 patients. In view of the advanced illness in this patient group we have allowed 20% attrition (phase II trial attrition from death or illness: 3/52) to the primary 12-week outcome, giving 296 patients, or 148 in each arm with both baseline and 12-week outcome data. The correlation between baseline and the 12-week outcome in the pilot study was 0.55. Using generalised linear model to adjust for the baseline score, with two-sided  $\alpha=0.05$  and correlation of 0.40, the study will have 80% power for a medium effect size of 0.30. To allow for heterogeneity across conditions and centres, we used conservative figures (eg. correlation 0.4 rather than 0.55; 20% attrition) to estimate the sample size. For the qualitative study, we estimate a sample size in each study site of seven patients/caregivers, total 35 patients/ caregivers in qualitative sample and six service providers/service commissioners from each site, total of 30 providers/commissioners. For the pilot phase we aim to recruit 15-25 patients/caregivers. The survey of health professionals will be primarily descriptive. It will be sent to a random sample of 200 health professionals, 40 in each area, with a mix of primary and secondary care staff identified as those referring to or interacting with SIPC. We estimate a response rate of 50-60% with 2 reminders giving at least 100 completed questionnaires.

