| Sample Size:                     | 356, 178 in each arm (short-term integrated palliative care vs standard care)                                                                                                                                                                                                                                                                                                                                                                                                                                                                                                                                                                                                                                                                                                                                                                                                                                                                                                                                                                                                                                                                                                                                                                                                                                                                                                                                                                                                                                                                                                                                                                                                                                                                                                                                                                                                                             |

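### Protocol section 20.1: 356 recruits, 20% attrition and 296 analysable patients do not agree; a 20% loss leaves about 285, with about 79% power (minor arithmetic error)

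*Protocol*

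**What the plan says.** Section 20.1 (Sample Size) states that "the five centres altogether need to recruit 356 patients", and the Study Synopsis repeats the target as "356, 178 in each arm (short-term integrated palliative care vs standard care"). The trial flowchart also shows 178 in each arm.

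On losses, section 20.1 allows 20% attrition, against 3/52 in phase II, "to the primary 12-week outcome, giving 296 patients, or 148 in each arm with both baseline and 12-week outcome data".

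The power statement follows directly. The model adjusts for the baseline score, the test is two-sided at 0.05, and with a "correlation of 0.40, the study will have 80% power for a medium effect size of 0.30". The same section reports a pilot correlation of 0.55. It describes both the 0.40 correlation and the 20% attrition as conservative choices, made to allow for heterogeneity across conditions and centres.

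**The concern.** The analysable number should follow from the recruitment target and the attrition rate, and here it does not. Taking 20% off 356 cannot give 296.

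The 80% power claim is tied to 148 per arm with complete data. If the attrition allowance has been misapplied, the power quoted does not belong to the attrition rate quoted beside it. Anyone comparing observed attrition with the planned 20%, for example the DMEC or the Study Steering Committee, would think the power target safe at any rate up to 20%. On the protocol's own inputs, the analysable number falls below 148 per arm once attrition passes about 17%. Attrition is a live question in this trial: section 20.1 justifies the allowance by the advanced illness of the patients.

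**Working it through.** **Inputs** (section 20.1 unless noted): 356 recruited, 178 per arm (also Study Synopsis); attrition 20%; 296 analysable, 148 per arm; baseline-adjusted model; two-sided alpha 0.05; correlation r = 0.40; standardised effect d = 0.30; power 80%; 1:1 allocation (section 16.4). For the sensitivity checks: pilot correlation 0.55 and phase II attrition 3/52.

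**Step 1: reproduce the protocol's power figure.** Adjusting for baseline multiplies the residual variance by 1 - r² = 1 - 0.16 = 0.84, so the residual SD is √0.84 = 0.9165.

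- Normal formula: n per arm = 2 x (1.960 + 0.842)² x 0.84 / 0.30² = 146.5, so 147.
- Power at 148 per arm: 80.4% (normal) or 80.1% (noncentral t, 2n - 3 degrees of freedom). By the t calculation 147 per arm gives 79.9%, so 148 is the smallest number that reaches 80%.

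The power step is therefore correct for 148 per arm, which leaves the attrition step as the source of the disagreement.

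**Step 2: check the attrition step.**

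- 356 x (1 - 0.20) = 284.8, so about 285 (142 to 143 per arm). The stated 296 is about 11 higher.
- Attrition implied by the stated figures: (356 - 296)/356 = 60/356 = 16.9%.
- Recruitment needed to keep 296 after a 20% loss: 296/0.80 = 370 (185 per arm), which is 14 more than planned.
- Multiplying instead of dividing: 148 x 1.2 = 177.6, rounded up to 178 per arm, or 356 in total. This reproduces the stated target exactly.

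**Step 3: power at the stated 20% attrition** (r = 0.40, d = 0.30, two-sided 0.05).

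| Analysable per arm | Power, normal | Power, noncentral t |
|---|---|---|
| 148 (as stated) | 80.4% | 80.1% |
| 142.4 (356 x 0.80 / 2) | 78.9% | 78.6% |
| 142 | 78.8% | 78.5% |

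The effect detectable with 80% power moves from 0.298 (normal) or 0.299 (t) at 148 per arm to 0.304 (normal) or 0.305 (t) at 142.4 per arm.

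**Step 4: how far the shortfall depends on the planning values** (noncentral t).

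- Correlation 0.55 with 142.4 per arm: 85.6%.
- Correlation 0.44 with 142 per arm: 80.1%, so a correlation only slightly above 0.40 restores the target.
- Attrition at the phase II rate, 3/52 = 5.8%: 356 x 49/52 = 335.5 analysable, and 84.8% power at r = 0.40.
- Attrition of 16.9%: 296 analysable and 80.1%, as the protocol states.

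**The case against.** The strongest reply is that this changes almost nothing. The gap is about 1.5 percentage points of power, and the detectable effect moves by about 0.006. It appears only if attrition reaches the full 20% and the correlation is as low as 0.40, and the protocol chose both values to be cautious. The allowance that 356 really provides, 16.9%, is still nearly three times the phase II rate of 5.8%, so calling it conservative against that benchmark remains fair. One caution is that phase II enrolled only patients with MS. This trial adds motor neurone disease and Parkinsonism and related disorders, so higher attrition than in phase II is plausible.

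All of this stands as an argument about size. It does not make the sentence correct: 356, 20% and 296 cannot all hold, and no other section of the protocol reconciles them.

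A reader might go further and infer that the trial is underpowered, or that it fails to deliver its 80% power. The documents do not support that. The target is missed slightly, at one conservative combination of inputs, and is met or exceeded at the pilot correlation or at attrition of about 17% or less.

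A reader might also take it as established that the authors multiplied by 1.2. The protocol shows no formula. The match to 178 per arm is exact and makes this the likely explanation, but it is an inference. On that reading the 20% is an uplift on the analysable number that has been described as a loss from the recruited number.

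**Conclusion.** The point holds as a minor arithmetic error. The analysable number in section 20.1 is wrong for the attrition rate stated with it: 20% attrition from 356 leaves about 285 patients, and 296 corresponds to 16.9%. On the planning values in section 20.1, and taking the comparison as a baseline-adjusted difference in means with equal arms, power at 20% attrition is about 79%. This is a correction to a stated figure. It is not a material loss of power, and it gives no reason to change the design or the recruitment target.

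**What to change.** Keep 356 and restate section 20.1 in one of two ways:

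- 356 recruits with 20% attrition give about 285 patients (about 142 per arm) and about 79% power for an effect of 0.30; or
- 356 recruits allow about 17% attrition, leaving 296 patients (148 per arm) and 80% power for an effect of 0.30.

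Either version replaces the statement that 20% attrition yields 296. If the second is chosen, the later mention of 20% attrition as a conservative figure in the same section should change to match. The Study Synopsis and flowchart need no edit, because they give only the recruitment figures.

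The cost is wording only, with no extra patients and no change to the analysis. The stated power or the stated attrition allowance becomes slightly less favourable.
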